# Counselling versus Low-Intensity Cognitive Behavioural Therapy for persistent sub-threshold and mild Depression (CLICD): study protocol for a pilot/feasibility randomised controlled trial

**DOI:** 10.1186/2193-1801-3-654

**Published:** 2014-11-05

**Keywords:** Depression, Primary care, Person-centred counselling, Low intensity cognitive behavioural therapy, Randomised controlled trial, Pilot study

## Abstract

**Background:**

Persistent sub-threshold depressive symptoms are important because almost all patients who experience symptoms for more than 2 years go on to develop major depressive episodes. The National Institute for Health and Care Excellence in the United Kingdom recommends research into the efficacy of person centred counselling and low-intensity cognitive behavioural therapy for persistent sub-threshold and mild depression.

**Methods/design:**

A two-arm, parallel group, pilot randomised trial to test the key components of trial delivery. The participants will be 50 patients with the diagnosis of persistent sub-threshold depressive symptoms and mild depression, recruited at five general practices in Glasgow, Scotland. Eligible patients will be randomised to receive either Person-Centred Counselling (PCC) or Low-Intensity Cognitive Behavioural Therapy (LI-CBT). The primary outcome measures are recruitment, adherence and retention rates at six months from baseline. The secondary outcome measures are changes at 6 months on GRID-HAMD-17; recovery from, or prevention of, depression according to DSM-IV diagnosis at 6 months; changes at 6 months on the PHQ-9, WSAS, EQ5D, and SF12v2 MH Enhanced.

We will provide estimates, with adequate precision, to help design future studies, of the recruitment rate and the proportion followed-up at 6 months; and identify potential moderators of outcome.

**Discussion:**

Evidence of comparative effectiveness of commonly used psychological treatments such as person-centred counselling and low intensity cognitive behavioural therapy is lacking in patients with sub-threshold and mild depression. This study will provide the information needed to construct a trial comparing these two treatments. This would help to inform early intervention treatment strategies for these conditions.

**Trial registration:**

Current Controlled Trials ISRCTN Register ID: ISRCTN60972025

## Introduction

Depression is a major public health problem that causes significant costs to individuals and society (Cassano and Fava 2002). It is associated with poor quality of life, impaired interpersonal and family relationships, occupational disadvantage, residual disability, and suicide (Thornicroft and Sartorius 1993). Almost 800,000 consultations for psychological signs and symptoms (mainly depression and/or anxiety) were conducted in general practice in Scotland in 2012 – 13 (Information and Statistics Division Scotland 2013). Persistent depressive symptoms below the threshold for major depression cause chronic illness and have a high risk of progression (Goldberg and Huxley 1992). Almost all patients with sub-threshold depressive symptoms lasting longer than 2 years eventually develop major depressive episodes (Klein et al. 2000).

### Rationale for the Study

The National Institute for Health and Care Excellence (NICE) (National Institute for Clinical Excellence 2009) recommends establishing if counselling and low-intensity cognitive behavioural interventions are effective alternatives to treatment as usual, in the management of persistent sub-threshold depressive symptoms and mild depression. Depressive symptoms are ‘persistent’, if they continue despite active monitoring and/or low-intensity intervention, or have been present for a considerable time. NICE recommends a non-inferiority trial design, using both observer and patient-rated assessments of improvement, and reporting short and medium-term outcomes of at least 18 months duration. The Scottish Intercollegiate Guidelines Network (SIGN) similarly recommends research on the long-term effectiveness of non-pharmaceutical interventions for depression (Scottish Intercollegiate Guidelines Network 2010).

Person-centred counselling (PCC), also known as non-directive therapy or Rogerian therapy, is the most common psychological intervention offered in community settings in the UK (Mellor-Clark et al. 2001). PCC focuses on providing an empathic, accepting, and genuine therapeutic relationship, which aims to foster clients’ inner capacities and resources, promoting positive change (Rogers 1951). Evidence, from a number of trials in the UK comparing counselling with usual GP care for patients with depression, suggests that counselling is superior to standard GP care with an effect size of 0.5 to 0.6, with the strongest effects in the short term (Bower and Rowland 2006).

Low intensity Cognitive Behavioural Therapy (CBT) guided self-help is recommended by NICE and SIGN for mild to moderate depression. Guided self-help CBT is considered a low intensity (LI) intervention because the amount of practitioner time is limited, compared to traditional high intensity (HI) expert-led treatments. Guided self-help CBT can be delivered through books, classes, computers and online resources (Williams and Morrison 2010). A review of the efficacy of treatments for depression found the overall effect of guided CBT self-help interventions was 0.8, (95% CI 0.58 – 1.01) with improved results when support or guidance was provided (Gellatly et al. 2007). A recent meta-analysis suggested equivalent outcomes for expert delivered CBT and for guided CBT self-help for depression (Cuijpers et al. 2010).

NICE also recommends assessment of the acceptability of the treatment options and the investigation of moderator variables affecting outcomes. A recent meta-analysis of patients’ preferences found that patients who were matched to their preferred talking therapy were less likely to drop out of therapy and had better outcomes (Swift et al. 2011). There is also a small but significant positive effect of patient prior expectation on successful treatment outcome (Constantino et al. 2011). In addition, about 85% of adults with depression experience significant symptoms of anxiety and their presence results in less positive treatment outcomes (Gorman 1997). Finally, patients with high alexithymia (i.e., difficulty in perceiving, differentiating, and expressing emotions) obtain less favourable outcomes from psychological therapies (McCallum et al. 2003).

## Methods/design

### Study Aims

This study aims to test the feasibility of a randomised controlled trial of the clinical and cost effectiveness of Low Intensity Cognitive Behaviour Therapy (LI-CBT) and Person-Centred Counselling (PCC) for patients with persistent sub-threshold depressive symptoms and mild depression. It will provide estimates for the recruitment, adherence, and retention rates, as well as estimates of the variability of outcome measures to inform power calculations for a definitive trial. Estimates of comparative intervention effects will be produced, but this study is not designed to have sufficient power to detect differences, nor to demonstrate non-inferiority between interventions. It will also:

Test the feasibility of measuring alexithymia, anxiety, preference for treatment, and outcome expectations as potential moderators of outcomes.Identify other factors that are potential moderators of outcomes.Test the feasibility of carrying out adherence/competence checks of the treatments delivered.Identify the feasible and necessary data to collect for a cost-effectiveness comparative analysis.

It will consider a range of variables at baseline as possible moderators (e.g., chronicity and severity of depressive symptoms and demographic variables). Finally, this study will help to identify any potential problems that will need to be addressed before a definitive trial.

### Type of study

This study is a two-arm, parallel group, randomised trial that will be performed according to the Research Governance Framework for Health and Community Care (Second edition, 2006) (Department of Health 2005). A two-arm design was adopted rather than a three-armed study with a control/usual care comparator. This was decided after discussion with the funder who was concerned that a three arm trial would be unnecessarily complex with little chance of testing out moderator variables. A two–arm study would have lower cost and more power to compare the relative cost-effectiveness of the interventions.

### Research questions

#### Primary research question

What are the likely recruitment, adherence, and retention rates over six months for a trial comparing PCC with LI-CBT in primary care for persistent sub-threshold and mild depression?

#### Secondary research questions

What sample size would be required for a larger comparative study of short-term (6 months) outcomes between PCC and LI-CBT in primary care for persistent sub-threshold and mild depression?What is the feasibility of measuring alexithymia, anxiety, preference for treatment, and outcome expectations as potential moderators of outcomes?What other factors can be identified as potential moderators of outcomes?What is the feasibility of carrying out adherence/competence checks of the treatments delivered?What data are feasible and necessary to collect for a cost-effectiveness comparative analysis?

### Outcome measures

The primary outcome measures are recruitment, adherence and retention rates at six months from baseline.

The secondary outcome measures are:Changes at 6 months on GRID-HAMD-17 (Williams et al. 2008)Recovery from, or prevention of, depression according to DSM-IV (American Psychiatric Association 2000) diagnosis at 6 months;Changes at 6 months on the Patient Health Questionnaire – 9 (PHQ-9) (Spitzer et al. 1999), Work and Social Adjustment Scale (WSAS) (Mundt et al. 2002), Euroquol (EQ5D) (The EuroQuol Group 1990), and SF12v2 MH Enhanced (Mariush and Turner-Bowker 2009

Evaluations at baseline, 3 and 6 months will all be conducted in person between the research assistant and subject and are summarised in Table 1.

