**Table 1 Tab1:** **Measures taken during the study**

Screening	Baseline	3 months	6 months
• PHQ-9.	• SCID interview	• PHQ-9	• PHQ-9
• Sociodemographic Questionnaire.	• GRID-HAMD-17	• SCID	• SCID
• Questionnaire for Non-Participants – reasons for not taking part.	• PHQ-9	• GRID-HAMD-17	• GRID-HAMD-17
	• GAD-7	• EQ-5D-5L	• EQ-5D-5L
	• WSAS	• SF-12v2 MH Enhanced	• SF-12v2 MH Enhanced
	• CSRI (baseline and demographics)	• WSAS	• WSAS
	• EQ5D-5L	• Adapted CSRI (employment)	• Adapted CSRI (employment)
	• SF12 v2 MH Enhanced	• Questionnaire for Research Evaluation	• Questionnaire: Prior Experience with Psychological Treatment
	• Toronto Alexithymia Scale	• CSQ-8	
	• Therapy Attitude Form	• Questionnaire Therapy Feedback	
		• Questionnaires for Non-Completers	
		• Change Interview (sub-sample)	

In addition to the primary and secondary outcome measures described above, we will also collect additional data to help us to assess the feasibility of the study and describe potential moderators. The measures used to collect these additional data include: a Sociodemographic Questionnaire for participants; a Questionnaire for Non-Participants about their reasons for declining participation; Structured Clinical Interview for DSM Disorders (SCID) interview (First et al. 1997); the Client Service Receipt Inventory (CSRI) (Chisholm et al. 2000); the Toronto Alexithymia Scale (Bagby et al. 1994); a Therapy Attitude Form to assess their prior views about therapy; a Questionnaire for Research Evaluation to assess views about the research process; Client Satisfaction Questionnaire version 8 (CSQ – 8) (Larsen et al. 1979); a Questionnaire for Non-Completers of the intervention to assess their reasons for non-completion; a Questionnaire for Feedback about their Therapy; a Change Interview with a subsample; and a Questionnaire about their Prior Experience with Psychological Treatment.

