### Participants and their recruitment

Fifty people with the diagnosis of persistent sub-threshold depressive symptoms and mild depression will be recruited at five general practices in Glasgow, Scotland. Eligibility to enter the trial will be confirmed at the baseline assessment by the researcher.

Identification of participants and screening for eligibility will occur in two stages:

(i). Participants will be initially screened at the GP practice by completing the self-report measure PHQ-9. Participants scoring 5–18 on the PHQ-9 (i.e. mild or moderate low mood) will be potentially eligible for the study. The GPs in the participating surgeries will be asked to screen the list of potentially eligible participants identified in their surgery to exclude anyone who meets the exclusion criteria for the study, or who they consider is unable to take part in either of the interventions.

(ii). The potentially eligible participants identified in the initial screening and not screened out by the GP, will attend the baseline assessment with a researcher. Eligibility to enter the trial will then be assessed by the researcher using a structured clinical interview (SCID).

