### Randomisation

At the end of the baseline assessment, all eligible and consenting participants will be randomly allocated by the researcher to one of the two treatments through a remote telephone randomisation system, after entering the necessary baseline participant information. Randomisation will be by means of a computer-generated code. Use of an automated telephone randomisation system will ensure concealment of allocation. Participants will be randomised individually in blocks of length 4, stratified by practice to balance practice level effects. The researcher will inform (eligible and consenting) patients of the outcome of randomisation at the end of the baseline interview.

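### The research role that obtains and announces the allocation also conducts the 3- and 6-month interviews, leaving the GRID-HAMD-17 and SCID outcomes open to unmasked rating

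*Protocol article*

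**What the plan says.** The Outcome measures section of the protocol article gives all three assessments to one role: "Evaluations at baseline, 3 and 6 months will all be conducted in person between the research assistant and subject". Table 1 lists the SCID and the GRID-HAMD-17 at baseline, 3 months and 6 months. The secondary outcomes include "Changes at 6 months on GRID-HAMD-17" and depression status by DSM-IV diagnosis at 6 months.

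The section on participants and their recruitment has the researcher carry out the SCID at the baseline assessment. The Randomisation section continues: "At the end of the baseline assessment, all eligible and consenting participants will be randomly allocated by the researcher to one of the two treatments". It then says: "The researcher will inform (eligible and consenting) patients of the outcome of randomisation at the end of the baseline interview". The related safeguard in that section is "Use of an automated telephone randomisation system will ensure concealment of allocation".

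At 3 months Table 1 also lists the therapy feedback questionnaire, the CSQ-8, the non-completer questionnaires and, for a sub-sample, the Change Interview. The Data analysis section commits to baseline-adjusted estimates of the difference between interventions with 95% confidence intervals.

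**The concern.** Concealment of allocation protects the trial up to the moment of randomisation. It does nothing about what the assessor knows afterwards. Here the stated procedure gives the arm to the research role that later interviews the patient for the GRID-HAMD-17 and the SCID. Both call for interviewer judgement, and both feed between-arm estimates that the article says will be produced. If the rater expects one therapy to do better, that expectation can enter the ratings. A confidence interval describes sampling error only and would not show it.

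The introduction and the Discussion also cite the guideline body's request for observer-rated as well as patient-rated assessment. In a comparison of two talking therapies the patient cannot be masked, so a masked rater is the main protection available for the observer-rated part. A pilot is a good place to find out how often such masking holds.

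**Working it through.** **Step 1: who does what**

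| Task | Role named | Where in the article |
|---|---|---|
| Baseline evaluation, in person | research assistant | Outcome measures |
| Baseline SCID for eligibility | researcher | Participants and their recruitment |
| Obtaining the allocation at the end of baseline | researcher | Randomisation |
| Telling the patient the arm | researcher | Randomisation |
| 3- and 6-month evaluations, including GRID-HAMD-17 and SCID | research assistant | Outcome measures; Table 1 |

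The two job titles meet at baseline. One section gives the baseline evaluation to the research assistant, and two others give the same assessment to the researcher. At the level of role, the terms therefore refer to the same function. The table follows a role and does not identify an individual.

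**Step 2: which outcomes are exposed**

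- Exposed: GRID-HAMD-17 (taken to be scored by the interviewer) and DSM-IV status (taken to come from the SCID, the diagnostic interview that Table 1 lists at follow-up).
- Not scored by the rater: PHQ-9, WSAS, EQ-5D and SF-12, which are patient-reported.
- Not dependent on the rater's scoring: recruitment, adherence and retention, the primary outcomes.

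**Step 3: the plan's own figure**

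The sample size section gives 0.91 SD as the detectable between-group difference with 20 per group and 80% power. Taking two-sided alpha as 0.05 (not stated), the noncentral t calculation gives 0.909 SD. The figure reproduces.

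**Step 4: scale of a possible shift**

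- Standard error of a difference in means, 20 per arm, without baseline adjustment: sqrt(2/20) = 0.316 SD.
- Half-width of the 95% interval: t(0.975; 38 df) × 0.316 = 2.024 × 0.316 = 0.64 SD.
- The article gives no size for rater bias. The values below are assumptions.

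| Assumed differential shift (SD) | Shift / 0.316 (standard errors) | Power of the study to detect a difference of that size |
|---|---|---|
| 0.1 | 0.32 | 6% |
| 0.2 | 0.63 | 9% |
| 0.3 | 0.95 | 15% |
| 0.4 | 1.26 | 23% |

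A shift anywhere in this range would move the GRID-HAMD-17 estimate and would be very unlikely to be noticed. A constant shift within an arm leaves the within-arm SD unchanged, so the variance estimate for planning the definitive trial is not affected by this form of bias.

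**The case against.** The strongest reply has four parts.

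1. **Identity.** The article uses two job titles and names no individual. With five practices, a colleague could do the follow-up of a patient whom someone else randomised. This stands, and it limits the point to roles. A reader might infer that the person who randomised a given patient always rates that patient later; the text does not establish this. It also does not require a different or masked rater, and the sequence of tasks is stated procedure.

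2. **Silence in a condensed article.** Masking details may sit in a fuller protocol. This stands as far as the mere absence of the word goes, and the point does not rest on it. It rests on the tasks that the article assigns.

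3. **The 3-month forms.** A reader might infer that the therapy questionnaires at 3 months would reveal the arm to any rater before the 6-month assessment. Table 1 gives neither the order of administration nor who reads the forms, and their contents are not shown. Disclosure is plausible, above all in the Change Interview, but that applies only to a sub-sample.

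4. **Limited consequence.** The study says that it is not powered for differences or for non-inferiority, the primary outcomes are not rated, both arms are active, and no direction of rater expectation is shown. All of this stands and lowers the priority. It does not remove the point, because the between-arm estimates will still be reported with intervals, and low power is no protection against bias.

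**Conclusion.** The point holds at role level. As written, the role that obtains and announces the allocation also conducts the follow-up interviews, and nothing stated separates the two tasks. GRID-HAMD-17 change and DSM-IV status at 6 months are therefore open to unmasked rating. This should be fixed because it is cheap; it does not threaten the study's main purpose.

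The size is conditional. An assumed differential shift of 0.2 to 0.3 SD equals 0.6 to 0.95 standard errors at 20 per arm, against an interval half-width of about 0.64 SD. Neither the shift nor its direction comes from the article. The conclusion also assumes that the GRID-HAMD-17 is interviewer-scored and that DSM-IV status is taken from the SCID.

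Two stronger readings are not supported. One is that the feasibility results are compromised: recruitment, adherence and retention do not depend on the rater's scores. The other is that the definitive trial will inherit unmasked rating: the article does not say that the arrangement will be reused, and one of its stated aims is to find problems to resolve beforehand.

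**What to change.** For participants not yet randomised:

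- Have the telephone system release the allocation to the trial office or the therapy provider, who tells the patient. The researcher receives only confirmation that randomisation is complete.
- At 3 and 6 months, complete the GRID-HAMD-17 and SCID before any therapy-related instrument, and ask the patient not to name the therapy.
- Have the therapy feedback, CSQ-8 and non-completer forms self-completed and returned sealed.
- At 6 months, record the rater's guess of the allocation or any unmasking, and report it as a feasibility result.

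For participants whose arm the rater already knows (the trial is ongoing), have a colleague who did not randomise them do the rating where more than one researcher is in post. Otherwise report those ratings as unmasked.

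Keep the Change Interview at 3 months, after the ratings, and note for that sub-sample that the rater may be unmasked at 6 months. Moving it beyond 6 months would protect masking but add a recall cost, since the counselling runs for eight weekly sessions.

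The cost is a changed notification route, a fixed visit order and short protocol wording, with no extra staff. The downside is that patients hear their allocation slightly later.

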**Table 1 Tab1:** **Measures taken during the study**

Screening	Baseline	3 months	6 months
• PHQ-9.	• SCID interview	• PHQ-9	• PHQ-9
• Sociodemographic Questionnaire.	• GRID-HAMD-17	• SCID	• SCID
• Questionnaire for Non-Participants – reasons for not taking part.	• PHQ-9	• GRID-HAMD-17	• GRID-HAMD-17
	• GAD-7	• EQ-5D-5L	• EQ-5D-5L
	• WSAS	• SF-12v2 MH Enhanced	• SF-12v2 MH Enhanced
	• CSRI (baseline and demographics)	• WSAS	• WSAS
	• EQ5D-5L	• Adapted CSRI (employment)	• Adapted CSRI (employment)
	• SF12 v2 MH Enhanced	• Questionnaire for Research Evaluation	• Questionnaire: Prior Experience with Psychological Treatment
	• Toronto Alexithymia Scale	• CSQ-8	
	• Therapy Attitude Form	• Questionnaire Therapy Feedback	
		• Questionnaires for Non-Completers	
		• Change Interview (sub-sample)	

In addition to the primary and secondary outcome measures described above, we will also collect additional data to help us to assess the feasibility of the study and describe potential moderators. The measures used to collect these additional data include: a Sociodemographic Questionnaire for participants; a Questionnaire for Non-Participants about their reasons for declining participation; Structured Clinical Interview for DSM Disorders (SCID) interview (First et al. 1997); the Client Service Receipt Inventory (CSRI) (Chisholm et al. 2000); the Toronto Alexithymia Scale (Bagby et al. 1994); a Therapy Attitude Form to assess their prior views about therapy; a Questionnaire for Research Evaluation to assess views about the research process; Client Satisfaction Questionnaire version 8 (CSQ – 8) (Larsen et al. 1979); a Questionnaire for Non-Completers of the intervention to assess their reasons for non-completion; a Questionnaire for Feedback about their Therapy; a Change Interview with a subsample; and a Questionnaire about their Prior Experience with Psychological Treatment.

